### Statistical Analysis

To assess differences between the Test-GA and Comparator-GA estimates, average difference (with standard deviations), intraclass correlation coefficient, paired *t*-testing, and Bland–Altman scatter plots [30] will be used. To evaluate the accuracy of Test-GA in identifying preterm and SGA neonates, sensitivity, specificity (with 95% confidence intervals), and receiver operating characteristic curves and other discriminant analysis techniques will be calculated. The relationship between the measurement of the newborn’s skin reflectance and newborn’s respiratory complications due to immaturity will be evaluated using receiver operating characteristic curves, association tests, and risk ratios. The significance level for hypothesis tests will be 5%, together with 95% confidence intervals.

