### Prior Work

The optical properties of the skin’s interaction with light can be evaluated by devices that emit and receive photons [13]. Variations in light scattering through the skin are believed to be associated with changes in skin thickness, the concentration of chromophores, and light wavelength [14]. A novel technology was developed to estimate GA at birth (Test-GA) by analyzing the photobiological properties of the newborn’s skin in combination with clinical variables [15]. This noninvasive and nonionizing technology features a probe containing light emitters and receivers that is brought in contact with the skin over the sole. A mathematical algorithm provides an estimated GA within seconds, combining the skin reflection with clinical adjusters, such as birth weight and incubator stay [15].

The timeline of the new medical device development involves sequential steps [16], represented in Figure 1. The prototype of the device previously evaluated 115 newborns at 24-41 weeks’ gestation with promising results [15]. After insights from this first clinical experiment published in 2017, the technology received improvements to mitigate external influences in the test, such as humidity, ambient light, and to ease the user handling. The current version is a small device, about the size of a pen, with an automated ability to measure skin reflection. To reduce examiner influence, the device now warns about errors of measurement. Clinical variables are presented in a digital screen immediately after the newborn skin assessment. Since February 2019, a clinical trial is taking place in 5 Brazilian hospitals to advance the GA prediction modeling, using a sample of 787 newborns [17]. The planned date of last enrollment is July 2020.

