### Present Protocol of Research

This protocol gathers data from Brazil and Mozambique referral centers. This step represents the clinical validation of the prediction model established in the preceding clinical trials. It aims to validate an optimized version of the device in low-resource birth settings, using a data set obtained in different populations, before introducing it in the market. The analysis relies on real-world antenatal GA estimations obtained during pregnancy in which first-trimester ultrasound may not always be available or reliable. The primary hypothesis of this study is that photobiological properties of the skin measured by the device, and adjusted by clinical variables, will allow the accurate prediction of GA (Test-GA) in low-birth-weight newborns.

The primary objective of this study is to validate the preemie test statistical model for GA estimation at birth and its accuracy to detect prematurity in low-birth-weight newborns. The secondary objective is to evaluate whether there is an association between skin reflection and the occurrence of early respiratory complications.

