### Data Definition and Collection

Comparator-GA is calculated by obstetric data obtained at the time of enrollment. The requirements for establishing the best GA calculation (assessed by interviewing the mother) are based on the following:

reliable last menstrual period dating, including certainty about last menstrual dating, regular menstrual cycles, no contraceptives within 3 months of conception, and no abortion or delivery 2 months prior to conception [18]; ORultrasound <24 weeks’ gestation, considered reference for low-income countries as recommended by the World Health Organization (WHO) [8], even if the clinical information on last menstrual period is absent.

For data curation, pregnancy dating based on ultrasonography reports will be adjusted to Intergrowth 21 standards. Fetal crown–rump length [23] as well as femur length and head circumference will be used to recalculate GA [24]. When both ultrasound and reliable last menstrual period dating are available, correction will depend on whether there are discrepancies in excess of 5, 7, 10, or 14 days according to the identified GA at first assessment as recommended in ACOG Committee Opinion guideline number 700 (May 2017) [6].

Test-GA will be determined by statistical analysis according to signals stored in the device’s processor and clinical data. For this, the GA modeling prediction is based on the result of another ongoing clinical trial (registration number RBR-3f5bm5). This study is taking place at 5 Brazilian centers with the analysis of the skin reflection and clinical data of 787 newborns, with 24-42 weeks of gestation, using strict rules of the crown–rump length ultrasound measurement for pregnancy dating [17]. We expect to establish the prediction model toward the end of the RBR-3f5bm5 clinical trial in September 2020.

Birth weight is the first measurement performed by the local staff during the first 24 hours of life. A digital scale for standardizing weighing is already present in all settings.

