### Study Outcomes

#### Primary Outcomes

The primary endpoints will be differences between the Test-GA and Comparator-GA estimates and proportion of correct preterm newborn detections by the Test-GA at <37 weeks’ gestation with a 1-week margin of error.

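### The tools fixed for the continuous primary endpoint do not assess calibration of Test-GA across the gestational age range, and the trend in a Bland–Altman plot should not stand in for it

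*Protocol article*

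**What the plan says.** Under Present Protocol of Research, the article states: "The primary objective of this study is to validate the preemie test statistical model for GA estimation at birth". It describes the study's place in the development programme in the same terms: "This step represents the clinical validation of the prediction model established in the preceding clinical trials". Test-GA is a model output (Prior Work): "A mathematical algorithm provides an estimated GA within seconds, combining the skin reflection with clinical adjusters, such as birth weight and incubator stay". The model comes from elsewhere (Data Definition and Collection): "the GA modeling prediction is based on the result of another ongoing clinical trial", a study of 787 newborns.

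The primary endpoints are "differences between the Test-GA and Comparator-GA estimates and proportion of correct preterm newborn detections by the Test-GA at <37 weeks’ gestation", the second with a 1-week margin. For the first, the Statistical Analysis section names the mean difference with its SD, the intraclass correlation, a paired t-test, "and Bland–Altman scatter plots [30] will be used". For preterm and SGA status it plans sensitivity and specificity with 95% confidence intervals, and ROC curves. It names no regression of Comparator-GA on Test-GA.

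**The concern.** A user of the device sees a Test-GA reading and wants to know the gestational age to expect at that reading. Validating a prediction model therefore includes calibration: over the range of readings, is the mean Comparator-GA equal to the reading? The four tools named for the continuous endpoint come from the comparison of two measuring methods. Only the Bland–Altman plot displays anything across the range, and its trend answers a different question.

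At stake is how the results are read. A sound model may appear to over-date the most preterm newborns and under-date the oldest. A model whose predictions are too widely spread in the new population may appear free of GA-dependent error. The study's purpose is to test the model in different populations and low-resource settings, so real failure to transport and ordinary regression to the mean need to be told apart.

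**Working it through.** **Inputs from the article.** n = 298 (Sample Size); the objective, endpoints and four tools set out above. The figure of 298 rests on accuracy of preterm detection. The minimum acceptable limit, power and preterm share behind it are not stated, so it cannot be rebuilt from the text. It serves here only as n.

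**Assumptions, not in the article.** SD of Comparator-GA 3 weeks (range 2.5 to 3.5); residual SD 1, 1.5 or 2 weeks (range 0.75 to 2); the Bland–Altman plot in its usual form, difference against average.

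**Notation.** P = Test-GA, Y = Comparator-GA, Y = a + bP + e, with e unrelated to P. Good calibration means a = 0 and b = 1. With D = P − Y and M = (P + Y)/2, the slope of D on M is

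2(Var P − Var Y) / (Var P + Var Y + 2 Cov(P,Y)).

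**Case 1: well-calibrated model.** Here Cov(P,Y) = Var P and Var P = 9 − Var e.

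- Residual SD 1: 2(8 − 9)/(8 + 9 + 16) = −0.061; times 5 weeks, 0.30 week.
- Residual SD 1.5: 2(6.75 − 9)/(6.75 + 9 + 13.5) = −0.154; 0.77 week.
- Residual SD 2: 2(5 − 9)/(5 + 9 + 10) = −0.333; 1.67 weeks.

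These are apparent biases at an average five weeks from the mean, although every reading is right on average. Over the whole assumed range the figure runs from about 0.1 week (SDs 3.5 and 0.75) to 3.1 weeks (SDs 2.5 and 2).

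**Case 2: predictions spread too widely, Var P = Var Y.** The numerator is zero, so the expected slope is zero. The true calibration slope is b = √(1 − Var e/9).

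- Residual SD 1: b = √(8/9) = 0.943; error in expected GA five weeks from the mean, 5(1 − 0.943) = 0.29 week.
- Residual SD 1.5: b = √(6.75/9) = 0.866; 0.67 week.
- Residual SD 2: b = √(5/9) = 0.745; 1.27 weeks.

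**Do the other three tools separate the cases?** Take residual SD 1.5 and equal means.

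- Intraclass correlation, approximated by 2 Cov/(Var P + Var Y): 13.5/15.75 = 0.857 in case 1 and 0.866 in case 2. It slightly favours the miscalibrated model.
- SD of differences: 1.50 against √(18 × (1 − 0.866)) = 1.55 weeks.
- Paired t-test: it sees mean bias only, and rejects in about 5% of simulated studies in both cases.

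**Simulation, n = 298, 1500 runs per setting.**

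| | Case 1 (calibrated) | Case 2 (too widely spread) |
|---|---|---|
| Trend against the average significant at 5% | 47–100% of runs | 4–6% |
| Test of calibration slope = 1 rejects | 4–6% | 45–100% |

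The ranges cover the whole assumed grid. The regression of Y on P gets both cases the right way round.

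**Precision of the calibration slope.** The 95% half-width is 1.96 × SD(e)/(√298 × SD(P)). At residual SD 1 it is 1.96/(17.26 × 2.828) = 0.04; at residual SD 2 it is 3.92/(17.26 × 2.236) = 0.10.

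**The case against.** The case on the other side is substantial, and most of it limits the point without removing it.

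- A reader might infer that the model is validated only by method-comparison tools, or not at all. The article does not support that. Sensitivity, specificity and ROC curves are planned for preterm status (a primary endpoint) and SGA. The mean difference is calibration in the large, and its SD describes prediction error.
- The article plans scatter plots. It plans no test of trend, and no recalibration based on one. This stands: the significance rates above describe a test that a reader of the plot might make, not a planned analysis.
- The trend is partly real. Among newborns of a given true GA, a calibrated prediction does over-date the most preterm; against Comparator-GA the slope is −(1 − R²). Apart from the share due to error in the comparator, that is genuine device error, and it is a legitimate thing to study. It is not miscalibration of the readings, and the plot cannot separate the two.
- The size is unknown. With a residual SD of 0.75 to 1 week the artefact is small, roughly 0.1 to 0.5 week five weeks from the mean. This stands.
- The article is condensed, and an unseen analysis plan may add calibration. Its absence alone would be no point. What remains is that the article itself selects the tools for this endpoint, and they do not match the objective it states.
- The article speaks of an algorithm and a prediction model, so calling it a regression would be an inference. The argument needs only Y = P + e for a calibrated prediction. It does not need predictions to vary less than outcomes in every new population.

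**Conclusion.** The point holds for the continuous primary endpoint. The four named tools assess mean bias and overall error, and none of them separates a well-calibrated Test-GA from one whose predictions are too widely spread. The trend in a plot against the average should not be used to judge GA-dependent miscalibration. With an assumed SD of Comparator-GA of 3 weeks, the misleading trend amounts to about 0.3, 0.8 and 1.7 weeks five weeks from the mean at residual SDs of 1, 1.5 and 2 weeks. The last exceeds 1 week, the margin that the article attaches to preterm detection. The real error that a flat plot can hide is 0.3, 0.7 and 1.3 weeks at the same residual SDs. Both sets rest on SDs that the article does not give.

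It would go too far to conclude that the Bland–Altman plot is wrong and must be dropped: it describes the differences that the endpoint names, and keeping it is a matter of preference. The sample size and the classification analyses are untouched.

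**What to change.** Keep the planned statistics. Add a regression of Comparator-GA on the locked Test-GA, that is, computed with the model taken over unchanged from the other trial. Report the calibration intercept and slope with 95% confidence intervals (targets 0 and 1), overall and by country. Show Comparator-GA minus Test-GA plotted against Test-GA. State that any conclusion about GA-dependent miscalibration of the model rests on this regression and not on the trend in the Bland–Altman plot.

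The cost is one regression and one plot on data already collected, with no extra newborns or procedures. Precision is adequate overall at n = 298. By country it will be lower: the split is not given, but with an assumed even split the half-width grows by √2, from 0.04–0.10 to about 0.06–0.14.

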## Methods

### Study Design

This protocol describes a multicenter prospective cohort study that aims to evaluate the ability of the preemie test device to estimate GA of low-birth-weight newborns. A nested case–control study will evaluate the relationship between the optical properties of the skin and newborn respiratory complications related to prematurity.

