### Eligibility Criteria and Participant Timeline

A sequential enrollment of newborns will follow the inclusion of participants based on eligibility criteria until the sample size is achieved. The inclusion criteria are liveborn infants weighing 500-2499 g with GA information obtained using a qualified last menstrual period or obstetric ultrasound <24 weeks’ gestation (Comparator-GA). Exclusion criteria are structural skin alterations or conditions that modify the skin, such as anhydramnios, hydrops, congenital skin diseases, and chorioamnionitis.

Table 1 illustrates the schedule of enrollment, test application, and endpoint measurement. The skin assessment will occur during the first 24 hours of age. The newborns will be followed up for 72 hours until discharge, held in hospital (for treatment-related purposes), or death, whichever occurs first, considered the study exit. The newborns will continue to receive standard assistance after the study follow-up according to settings, resources, and local staff definitions, whether during hospital admission or at hospital discharge or re-admission.

**Table 1 table1:** Participant timeline of the study.

Study procedures	Before Test-GA	Test-GA, ≤24 hours old	72 hours old: discharged, held in hospital, or death
Enrollment 1: Prospective cohort study^a,b^	X		
Informed consent	X		
Taking of obstetric history	X		
Intervention: Test-GA		X	
Comparator: Best estimation of GA available		X	
Enrollment 2: Nested case–control study^c^			X
Assessments and analysis^d^			X

^a^Inclusion criteria are liveborn, Comparator-GA (reliable last menstrual period [18] or ultrasound assessment at <24 weeks’ gestation [8]), birth weight (500-2499 g), and ≤24 hours old.

^b^Exclusion criteria are malformation with structural skin alterations and skin modifiers (eg, anhydramnios, hydrops, congenital skin diseases, chorioamnionitis).

^c^To determine eligibility criteria for paired allocation according to birth weight range to either the case group (TTN or RDS) or the control group (without TTN, RDS, tachypnea due to other reasons, or bloodstream infection).

^d^Neonatal outcomes including respiratory complications due to prematurity, neonatal intensive care unit admission, or ventilatory support

GA: gestational age; RDS: respiratory distress syndrome; TTN: transitory tachypnea of the newborn.

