Within the study cohort, a secondary nested case–control study will include newborns with the following inclusion criteria: (1) for the case group, respiratory distress syndrome or transitory tachypnea of the newborn; (2) for the control group, newborns will be randomly selected with no respiratory diseases or manifestations by other conditions, paired by birth weight range: <1000 g, 1000-1499 g, or 1500-2499 g.

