#### Secondary Outcomes

The secondary endpoint will be the proportion of correctly identified SGA newborns under the tenth percentile of GA according to Intergrowth 21 standards [25]. For this endpoint, the proportion of SGA newborns detected by the Test-GA will be compared with that detected by the Comparator-GA.

Others secondary endpoints in the case–control nested study will be the capacity of the Test-GA results to predict the following neonatal complications:

Respiratory distress syndrome based on clinical and radiological findings and respiratory outcomes [26,27].Transitory tachypnea of the newborn based on clinical findings and respiratory outcomes [26].Ventilatory support due to pulmonary immaturity.Neonatal intensive care unit admission for pulmonary immaturity.

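### Respiratory endpoints: risk ratios and ROC curves are planned in a case–control sample paired by birth weight, with no weighting or matched analysis, although the whole cohort is measured

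*Protocol article*

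**What the plan says.** All references are to the protocol article.

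- **Study Design:** "A nested case–control study will evaluate the relationship between the optical properties of the skin and newborn respiratory complications related to prematurity".
- **Secondary Outcomes:** further "endpoints in the case–control nested study will be the capacity of the Test-GA results to predict" respiratory distress syndrome (RDS), transitory tachypnea (TTN), and ventilatory support and intensive care admission for pulmonary immaturity.
- **Eligibility Criteria and Participant Timeline:** cases have RDS or TTN. For controls, "newborns will be randomly selected with no respiratory diseases or manifestations by other conditions", and they are "paired by birth weight range: <1000 g, 1000-1499 g, or 1500-2499 g". Table 1, footnote c, describes the control group as "without TTN, RDS, tachypnea due to other reasons, or bloodstream infection". No case:control ratio is given.
- **Statistical Analysis:** the relation between skin reflectance and respiratory complications "will be evaluated using receiver operating characteristic curves, association tests, and risk ratios". The section mentions no sampling weights, matched analysis or odds ratio.
- **Prior Work:** birth weight is one of the clinical adjusters in the algorithm that produces Test-GA.
- **Table 1 and its text:** the device reading is planned by 24 hours of age, and follow-up to 72 hours or earlier exit, for the whole cohort. Respiratory complications, intensive care admission and ventilatory support are among the outcomes assessed.
- **Abstract, Objective:** the aim is to predict short-term pulmonary complications in a cohort of low-birth-weight newborns.

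**The concern.** The listed measures do not fit the sample they are assigned to. A risk ratio compares the proportion of infants who develop the outcome. In a case–control sample the investigators set the overall proportion of cases when they choose how many controls to take, so an unweighted ratio of proportions reflects that choice as well as biology.

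The ROC curve has a different problem. Random sampling of controls alone would leave it unbiased, because sensitivity and specificity are conditional on outcome status. Here the controls are made to resemble the cases on birth weight, which tracks gestational age and enters Test-GA, and some non-cases are barred from selection. The curve then refers to neither the enrolled cohort nor any other clinical population.

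At stake is the only secondary objective named in the Introduction (Present Protocol of Research). A reader would take the published risk ratio and AUC as describing low-birth-weight newborns in these hospitals.

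**Working it through.** **No stated figure to reproduce.** The protocol gives no respiratory event rate, case:control ratio, expected risk ratio or AUC. The 298 rests on the primary endpoint and serves here only as a scale. All risks below are assumptions.

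**1. Risk ratio with one control per case.** Assume 298 newborns in two equal groups by device reading, with risks of 50% and 20%. The controls are a simple random sample of non-cases, which isolates the effect of sampling.

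- Cases: 149 × 0.50 = 74.5 and 149 × 0.20 = 29.8; total 104.3.
- Non-cases: 74.5 and 119.2; total 193.7.
- True risk ratio: 0.50 / 0.20 = 2.5.
- Fraction of non-cases sampled: 104.3 / 193.7 = 0.538.
- Controls drawn: 74.5 × 0.538 = 40.1 and 119.2 × 0.538 = 64.2.
- Apparent risk ratio: (74.5 / 114.6) / (29.8 / 94.0) = 0.650 / 0.317 = 2.05.
- Odds ratio in the sample: (74.5 × 64.2) / (40.1 × 29.8) = 4.0. In the cohort: (74.5 × 119.2) / (74.5 × 29.8) = 4.0.
- Newborns used: 2 × 104.3 ≈ 209 of 298.

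**2. Dependence on the ratio.** Assume a 10% baseline risk, a true risk ratio of 3.0 and equal groups. Per 100 in each group there are 30 and 10 cases, and 70 and 90 non-cases (40 and 160 in total). The odds ratio is (30 × 90) / (70 × 10) = 3.86 throughout.

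| Controls per case | Non-cases sampled | Apparent risk ratio |
|---|---|---|
| 1 | 40/160 | (30/47.5)/(10/32.5) = 2.05 |
| 2 | 80/160 | (30/65)/(10/55) = 2.54 |
| 4 | 160/160 | (30/100)/(10/100) = 3.00 |

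The cohort value returns only when every non-case is taken.

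**3. Weighting.** In example 1, weighting each control by 193.7 / 104.3 = 1.857 restores 74.5 and 119.2 non-cases, and hence 2.5. The information exists because the cohort is enumerated. The weights cannot restore infants who could never be chosen as controls.

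**4. ROC curve, effect of pairing.** A simulation drew 1,000,000 newborns, kept those of 500–2499 g, and compared the full cohort with a 1:1 sample matched on the three weight bands. Assumed complication rates ran from 15% to 50%, and birth weight supplied 0–40% of Test-GA.

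| | Full cohort | Matched sample |
|---|---|---|
| AUC | 0.66–0.77 | 0.59–0.68 |
| Risk ratio, Test-GA <34 weeks | 1.64–4.88 | 1.41–1.90 |

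The AUC fell in every scenario, by 0.05 to 0.14. It fell even with birth weight given no share of Test-GA, because birth weight and gestational age are related. The growth and risk models are assumed, so these ranges show the direction of the matching effect and do not forecast its size.

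**5. ROC curve, effect of the control restriction.** Infants with other tachypnea or bloodstream infection are neither cases nor controls. If they are harder to separate from cases than healthy infants, leaving them out raises the AUC. The simulation did not include this, so the net effect of pairing and restriction is not determined.

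**The case against.** **The protocol may intend something valid.** Statistical Analysis does not name the case–control sample, and an article can leave weights and analysis sets to a fuller plan. That is fair as far as it goes. But the Abstract, Study Design and Secondary Outcomes all place the respiratory question in the case–control study, and no section assigns it to the cohort. Read as written, the listed measure does not suit the listed design.

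**The risk ratio can be recovered.** A reader might infer that a risk ratio is not estimable at all. The documents do not support that: sampling is within an enumerated cohort, so the fractions will be known and weighting works. The fault is the absence of any such step beside a plainly listed risk ratio.

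**Pairing can be defended.** Study Design and Statistical Analysis name skin reflection as the predictor, while Secondary Outcomes names Test-GA. If the question is what reflectance adds beyond weight, matching on weight is reasonable, given an analysis that respects it. The bands are also wide, one spanning 1500–2499 g, so weight is only partly balanced. It is therefore too strong to call the AUC meaningless; it answers a different question. The stated aim, however, is prediction in the cohort, and no section mentions added value over birth weight.

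**Clean controls reduce misclassification.** The Discussion expects chest X-ray to be unavailable at times, so setting aside doubtful infants has a rationale. Ventilatory support and intensive care admission are defined as due to pulmonary immaturity and should largely overlap with RDS and TTN. Both points soften the concern about selection but do not make the sample represent the cohort.

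**Completeness.** Outcomes for all newborns are what is planned; some infants may exit before 72 hours.

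**Conclusion.** The concern holds in limited form. Taken as written, the plan yields a risk ratio that moves with the case:control ratio (2.05 against a true 2.5 in the worked example, odds ratio 4.0 in both) and a ROC curve that does not describe the cohort in the objective. The dependence on the sampling ratio is general; the figures rest on assumed risks.

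Two further inferences are not supported. One is that the AUC will be understated by a known amount: pairing and control restriction can pull in opposite directions. The other is that a particular share of cases will go unpaired in the lightest bands: this happened at the higher assumed event rates, but the protocol gives none.

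The primary endpoints and the sample size are unaffected, and the cohort data remain available. This should be fixed before the respiratory analysis; it does not threaten the study.

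**What to change.** 1. **Main analysis in the full cohort.** Estimate risk ratios (log-binomial or modified Poisson regression) and ROC curves in all enrolled newborns for RDS or TTN combined, ventilatory support, and intensive care admission.
2. **RDS and TTN separately.** State how infants with the other diagnosis are handled. Counting them as ordinary non-cases would blur both curves.
3. **Value beyond birth weight, if wanted.** Make it a separate analysis, using skin reflectance adjusted for birth weight or a covariate-adjusted ROC curve. Adjusting Test-GA for birth weight in the main analysis would condition on one of its own inputs.
4. **If the matched sample is kept.** Report odds ratios from a matched or band-adjusted logistic model, or risk ratios and ROC curves weighted by the known sampling fractions. Say that the weighted results exclude infants who could be neither case nor control.

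The cost is a change of analysis wording and slightly more analysis work, with no new data. The AUC may look less favourable once infants with other respiratory problems count as non-cases.

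### Risk ratios are planned for respiratory endpoints that sit in a nested case–control sample, where an unweighted risk ratio does not estimate the cohort risk ratio

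*Protocol article*

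**What the plan says.** All references are to the Methods of the protocol article.

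- **Study Design** gives the respiratory question its own design: "A nested case–control study will evaluate the relationship between the optical properties of the skin and newborn respiratory complications related to prematurity".
- **Secondary Outcomes** places the respiratory endpoints there: "Others secondary endpoints in the case–control nested study will be the capacity of the Test-GA results to predict the following neonatal complications". The list is RDS, TTN, ventilatory support and intensive care admission for pulmonary immaturity.
- **Eligibility Criteria and Participant Timeline** selects on outcome: "for the case group, respiratory distress syndrome or transitory tachypnea of the newborn"; and "for the control group, newborns will be randomly selected with no respiratory diseases or manifestations by other conditions, paired by birth weight range". The three ranges are below 1000 g, 1000–1499 g and 1500–2499 g. No number of controls per case is given.
- **Table 1** puts this second enrolment at the 72-hour or exit column, when outcomes are known. Its note c describes the step: "To determine eligibility criteria for paired allocation according to birth weight range to either the case group (TTN or RDS) or the control group". The same note keeps newborns with tachypnea from other causes, or with bloodstream infection, out of the control group.
- **Statistical Analysis** says that the relationship between skin reflectance and respiratory complications "will be evaluated using receiver operating characteristic curves, association tests, and risk ratios".

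**The concern.** The effect measure does not fit the sample. When all cases and only some non-cases are taken, the share of affected newborns is set by the investigators. With k controls per case it is 1/(1+k), so 50% at 1:1, whatever the incidence in the cohort. A risk computed in that sample is not a newborn's risk, and a ratio of two such risks is not the cohort risk ratio.

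At stake is the size of the association reported for the protocol's stated secondary objective. Two teams with the same cohort and the same device readings would publish different risk ratios if they drew different numbers of controls. Pairing by birth-weight range adds a second source of distortion: the fraction of non-cases drawn can differ between bands, so a crude ratio over the pooled sample mixes bands with different sampling fractions.

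**Working it through.** **Plan's own figure.** The protocol gives no number for the respiratory analysis, so there is none to reproduce. Its total of 298 belongs to the primary accuracy endpoint and is used here only as the cohort size; the ratios below do not depend on it.

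**Inputs**
- From the protocol: N = 298; all cases kept; controls sampled at random from the unaffected.
- Assumed, since the protocol gives none: half the newborns have immature skin reflectance (exposed); the complication risks shown below; k controls per case; one sampling fraction for all non-cases, ignoring bands and the control exclusions.

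**Formulas.** Let a and c be exposed and unexposed cases, and b and d exposed and unexposed non-cases. The fraction of non-cases sampled is f = k(a+c)/(b+d).
- Cohort risk ratio: [a/(a+b)] / [c/(c+d)]
- Unweighted sample risk ratio: [a/(a+fb)] / [c/(c+fd)]
- Odds ratio: ad/(bc); f cancels
- Weighted risk ratio: each control counts 1/f, which restores b and d and so the cohort value

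The sample risk ratio can be written (a/c)(c+fd)/(a+fb). It equals 1 at f = 0 and the cohort risk ratio at f = 1. Its slope in f has the sign of ad − bc, so it moves steadily from one to the other. With a single f the distortion is therefore always towards 1.

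**Worked case, risks 50% vs 15%.** There are 149 newborns per group.
- a = 74.5, b = 74.5, c = 22.35, d = 126.65; 96.85 cases and 201.15 non-cases.
- Cohort risk ratio: 0.50/0.15 = 3.33. Odds ratio: (74.5 × 126.65)/(74.5 × 22.35) = 5.67.
- k = 1: f = 96.85/201.15 = 0.481; fb = 35.9, fd = 61.0; (74.5/110.4)/(22.35/83.3) = 2.52.
- k = 2: f = 0.963; fb = 71.7, fd = 122.0; (74.5/146.2)/(22.35/144.3) = 3.29.

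**Other assumed risks**

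| Risks | Cohort RR | OR at any k | k = 0.5 | k = 1 | k = 2 | k = 4 |
|---|---|---|---|---|---|---|
| 15% vs 5% | 3.00 | 3.35 | 1.56 | 1.91 | 2.31 | 2.68 |
| 50% vs 20% | 2.50 | 4.00 | 1.64 | 2.05 | not possible | not possible |
| 70% vs 30% | 2.33 | 5.44 | 1.78 | 2.33 (f = 1) | not possible | not possible |

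Not possible means there are too few non-cases. In the last row 1:1 sampling takes every non-case, so nothing is lost. The odds ratio stays constant but is not a substitute for the risk ratio when the outcome is common: 4.00 against 2.50 in the second row, but 3.35 against 3.00 in the first.

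**The case against.** **The sentence may refer to the full cohort.** The Statistical Analysis sentence does not name the nested sample. The Objective speaks of prediction in a cohort, and Table 1 lists respiratory outcomes in a row separate from the second enrolment. A cohort risk ratio is compatible with that. It is the less natural reading, because Study Design and Secondary Outcomes both put this question in the case–control study. If it was the intention, one sentence settles it.

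**Weights can be left to the analysis plan.** This is fair, and their absence is not the point. The point is that the article names a measure which, taken as it stands, does not fit the design it describes.

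**The error can be small.** This is true. At 50% vs 15% with two controls per case, 3.29 against 3.33 is about 1% low. The more common the outcome, the larger the share of non-cases that a given number of controls per case takes up, and the smaller the distortion.

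**Stronger readings that the documents do not support.**
- A reader might infer that the sample risk ratio says nothing about newborn risk. It still carries the association, but in distorted form.
- A reader might infer that absolute risks and predictive values for respiratory outcomes would be wrong too. None is planned in Statistical Analysis, and the Discussion voices only a belief that the device could help to identify newborns who need support.
- A reader might take it as given that RDS or TTN is common below 2500 g. The protocol states no incidence, so this remains an assumption.
- A reader might extend the fault to the ROC curves. Sensitivity and specificity are computed within cases and within controls, so the control ratio does not bias them in this way.

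**Conclusion.** The point holds as a mismatch between design and effect measure. If the risk ratio is computed unweighted in the nested sample, it does not estimate the cohort value unless all non-cases are taken.

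The size depends on quantities that the protocol does not give. At one control per case the shortfall is 24% (2.52 against 3.33) for risks of 50% vs 15%, 36% (1.91 against 3.00) for 15% vs 5%, and nil for 70% vs 30%. These figures assume half the newborns exposed and one sampling fraction throughout. Band-specific fractions could change a crude ratio further, and no figure is offered for that.

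This should be fixed, but it is not critical. It concerns one of three listed tools for a secondary objective. Both primary endpoints, the SGA comparison and the sample size are untouched.

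**What to change.** In Statistical Analysis:

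1. For the nested sample, replace risk ratios with odds ratios from logistic regression conditional on birth-weight band, and state that they are not to be read as risk ratios if the outcome proves common.
2. Report risk ratios only from the full cohort (log-binomial or modified Poisson regression, with the outcome taken to study exit as defined under Eligibility Criteria and Participant Timeline) or from the nested sample with inverse-sampling-fraction weights by band. Study exit can come before 72 hours through discharge or death, so a complete 72-hour outcome should not be presumed.
3. State the comparison group. The full cohort includes newborns barred from the control group (other tachypnea, bloodstream infection); a weighted nested analysis does not bring them back.
4. Ventilatory support and intensive care admission do not define the cases, so an odds ratio for them in a sample selected on RDS or TTN is not protected in the same way. Analyse these two in the full cohort or with the weights.

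The cost is a few sentences in the analysis section. The cohort is enumerated, and device readings and follow-up to study exit are already planned for it, so no new data are needed.
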